### Blinding

3.9

Due to the nature of ear molding, it is impossible to blind the interventionist, participants and their parents. Therefore, assessor blinding will be used for the primary outcome physician assessment of improvement and secondary outcome WPU index score.

### Sample size

3.10

The test level α is 0.05, and the statistical power is (1- β) is 0.9. According to literature reports, the effective rate of ear mold correction within 2 weeks of age was about 90%, and the natural improvement rate without intervention was about 70%. The sample content was calculated to be 79 cases per group. According to the possible loss of follow-up of 20%, the sample was expanded to 95 cases in each group, with a total of 190 cases in both groups.

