## Introduction

1

Congenital auricular deformities (CAD) or congenital ear malformation are common in children. However, the prevalence of CAD is varied surprisingly from 1.7% to 50% among different populations,^[1–5]^ which may at least partially due to definition and diagnosis criteria. CAD will not only affect the appearance, but also hearing and mental health of the child. Parents’ mental health and quality of life may also be affected. Observational study has shown that about 70% infants with CAD at birth will recover naturally at 1 years old, but who will recover spontaneously is unclear.^[3]^

Traditional treatments for CAD are mainly surgical, which normally be arranged at around 6 years old.^[6]^ They are invasive and painful by its nature, and complications are not rare,^[7]^ including hematoma, infection, bleeding, allergic reactions, and necrosis, hypertrophic scars, keloids, fistulae, and recurrence.^[8]^ What is more, impairment of hearing or mental health of the child affected may already happened, which may have life-long consequences.^[9,10]^ Additionally, surgeries and subsequent care are expensive, bringing considerable economic burden to the family and society.

Non-surgical interventions of CAD were initialized in the 1980s.^[11]^ They are attractive for many health professionals and patients for the noninvasive nature, relatively easy process, sound curative rate and low cost compared with surgeries. At the primitive stage, doctors used tape and stick to shape the ear of children with CAD and found promising results, but highly relied on the skills of the doctors.^[12,13]^ Tape and stick were evolved to ear molding which increased the standardization of the treatment in recent decade.^[14]^ Studies found that the effectiveness rate of ear molding for CAD was up to 90%, and earlier intervention could lead to better outcomes, with few adverse events.^[15–19]^ However, these studies are mainly observational study or noncontrolled study, fall short of methodological rigour and prone to biases. As far as we know, there has been no randomized controlled trial (RCT) evaluating the effectiveness, safety and cost-effectiveness of ear molding for CAD and.

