#### Primary outcome

3.8.1

*Physician assessed improvement.* Two doctors who do are unaware of the group assignment of participants will assess the improvement of auricular form independently. Standardized photographs of participants’ ears will be obtained and assessed using the West China-Peking Union (WPU) index for CAD designed by the research team for the study (see supplementary Table 1 and supplementary Figure 1). Standardized photographs of ears will be obtained by the following way:

(1)Photographs will be obtained at the following anatomical position: upright (showing binaural), fully lateral (showing monaural), lateral 45 degrees (showing monoaural), posterior (showing binaural), and axial position (showing binaural) Among them, the full lateral position and the lateral 45-degree position are about 25 cm from the ear surface;(2)both ears will be photographed in the lateral position and the lateral 45-degree position to facilitate the comparison of the auricle shape;(3)Photographs should clearly and fully show the shape of the auricle, multiple photographs at one angle (1–3 photographs) can be taken for this purpose.

The average score of the 2 physicians’ assessment will be used to calculate the improvement value using the following formula: Improvement value = (total follow-up score — total baseline score) / total baseline score.

The effect size of the improvement value of 0.1 or less will be defined as ineffective, 0.1 to 0.3 as small, 0.3 to 0.5 as medium, and >0.5 as significant. Ineffective and small effect will be classified as nonsignificant improvement (0), and medium or significant effect will be classified as significant improvement (1), turning the effect size into a dichotomous variable, upon which the improvement rate will be calculated.

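### The stated 90% power is unsupported for the trial's own endpoint: the 70% control rate matches only a 1-year recovery figure, and neither planning rate is on the WPU responder endpoint

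*Protocol article*

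**What the plan says.** Section 3.10 (Sample size) gives four inputs: "The test level α is 0.05"; "the statistical power is (1- β) is 0.9"; for the molding arm, "the effective rate of ear mold correction within 2 weeks of age was about 90" per cent; and for the control arm, "the natural improvement rate without intervention was about 70" per cent. Both rates are attributed to literature reports, without a citation, an outcome definition or a time point for the control figure. The result is 79 per group, raised to 95 per group (190 in all) for 20% loss to follow-up.

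Section 1 (Introduction) has the only other statement of a 70% natural course: "about 70% infants with CAD at birth will recover naturally at 1 years old". On molding it says that "the effectiveness rate of ear molding for CAD was up to 90" per cent and that earlier treatment could do better. It then says of this evidence that "these studies are mainly observational study or noncontrolled study, fall short of methodological rigour and prone to biases".

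Section 3.8.1 defines the primary outcome from blinded photograph ratings on the "West China-Peking Union (WPU) index for CAD designed by the research team for the study". An infant counts as improved when the score gain relative to baseline is medium or significant, that is, above 0.3. Section 3.8.2 gives the index a range of 0 (worst) to 100 (best) and sets measurements at 3 and 12 weeks after treatment. Sections 3.5 and 3.6 end follow-up at 6 weeks, and section 3.6 then offers molding to controls who have not recovered.

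**The concern.** A sample size calculation supports a trial's power only if its event rates refer to the endpoint that will be analysed, at the time it will be analysed. Here the control rate matches a 1-year figure, while controls are planned to stay untreated for 6 weeks. That figure also describes recovery, whereas the trial counts a relative score gain above a threshold. The molding rate comes from literature that predates the index, so it cannot be on the index either.

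At stake is how far the 90% can be relied on. If it is taken at face value, a null result would be read as good evidence against a worthwhile effect, although the true power for this endpoint could be well below or well above 90%.

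**Working it through.** **1. Reproduce the plan's figure.** Inputs from section 3.10: rates 0.90 and 0.70, alpha 0.05, power 0.90, equal groups. Sidedness is not stated; two-sided reproduces the result. With the unpooled formula

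n = [p1(1−p1) + p2(1−p2)] × (z_0.975 + z_0.90)² / (p1−p2)²

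= (0.09 + 0.21) × (1.960 + 1.282)² / 0.20² = 78.8, so 79 per group. This matches. The arcsine formula gives 78.995, also 79. The arithmetic is not in question.

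**2. Compare the inputs with the endpoint.**

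| | Planning figures | Primary endpoint |
|---|---|---|
| Control, time | No time in 3.10; the only matching figure (section 1) is at 1 year | 3 and 12 weeks after treatment (3.8.2); follow-up ends at 6 weeks (3.5, 3.6) |
| Control, measure | Natural improvement (3.10); natural recovery (section 1) | Relative WPU gain above 0.3 |
| Molding, measure | Effective rate in the literature | Relative WPU gain above 0.3 |
| Evidence | Molding studies mainly observational or noncontrolled (section 1) | Blinded, randomised comparison |

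The schedule statements disagree with each other, but the mismatch does not depend on which one stands. Counted from the end of a 2-week course, even the later visit falls at about week 14 (2 + 12), far short of 1 year.

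The measure matters as well as the time. With a maximum score of 100, a relative gain above 0.3 is impossible when the baseline exceeds 100/1.3 = 76.9, even with complete recovery. A literature rate of recovery or effectiveness therefore need not carry over to this endpoint in either arm.

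**3. Sensitivity of power to the rates.** With n = 79 per arm,

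power = Φ( |p1−p2| / √{[p1(1−p1) + p2(1−p2)]/79} − 1.960 ).

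For example, 0.85 vs 0.70: √(0.3375/79) = 0.0654; 0.15/0.0654 = 2.295; Φ(0.335) = 0.63.

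| Molding | Control | Power, unpooled | Power, pooled |
|---|---|---|---|
| 90% | 70% (plan) | 90% | 88.9% |
| 90% | 60% | over 99% | 99.5% |
| 90% | 50% | over 99% | about 100% |
| 85% | 70% | 63% | 61.9% |
| 80% | 70% | 31% | 30.4% |
| 80% | 60% | 80% | 78.9% |
| 70% | 50% | 75% | 73.2% |

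All rates other than 90% and 70% are assumptions chosen to show the range; the document gives none. Lowering only the control rate raises power. Lowering only the molding rate reduces it. Lowering both while keeping the 20-point difference also reduces it, because the variance grows as the rates move towards 50%.

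**The case against.** The strongest reply is that the time-point error, taken alone, is conservative. If fewer controls have improved within weeks than within a year, the difference from molding widens and power rises. This stands. The low-power rows need a separate assumption that molding does less well than 90%, and no figure in the document supports 80% or 85%. A reader might infer from those rows that the trial is underpowered; the document does not show that.

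A second reply concerns the 90%. A reader might infer that section 3.10 recast an upper limit in the Introduction as a typical value. But section 3.10 speaks of correction within 2 weeks of age, section 1 says that earlier treatment may do better, and section 3.5 starts molding within 3 days of birth. A rate of about 90% in infants treated early is compatible with an overall maximum of 90%, so that charge does not hold. What remains is that the evidence is, in the protocol's own words, weak, and that it is not on this endpoint.

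Third, section 3.10 cites no source, so tying its 70% to the Introduction is an inference. It is a fair one, since no other 70% natural-course figure appears in the document.

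Two further readings go too far. A reader might interpolate the 1-year figure to an early control rate, but the document gives no time course, and recovery is not the responder endpoint. A reader might also expect the trial to present an early difference as lasting deformity avoided; neither the Objective nor the Discussion says so, and section 3.6 allows for spontaneous recovery.

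Finally, borrowing literature rates for a new instrument is common and sometimes unavoidable. That excuses using them as a starting point. It does not excuse quoting one power figure as if they applied directly.

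**Conclusion.** The point holds in this limited form: the stated 90% power is not supported for the trial's own endpoint and time, and the direction of the error is unknown. The calculation is correct for the rates it uses, but those rates describe other outcomes and, for the controls, as far as the document shows, a much later time. Over the illustrative range in which at least one rate departs from the plan, power at 79 evaluable infants per arm runs from 31% (80% vs 70%) to over 99% (90% vs 50%). This rests on a two-sided 0.05 test, simple two-proportion formulas, assumed alternative rates, and the inference that the 70% in section 3.10 is the 1-year figure in section 1. No single corrected sample size can be derived, because the document contains no rates on the WPU responder endpoint.

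**What to change.** First reconcile the statements in sections 3.5, 3.6 and 3.8.2 on 3 weeks, 12 weeks and 6 weeks of follow-up, and name the primary time point. Then revise section 3.10 to:

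- say that the 70% is a 1-year natural recovery figure, or cite the different source if there is one;
- state the control and molding rates assumed for a relative WPU gain above 0.3 at the primary time point, marked as assumptions where no data exist;
- replace the single 90% with power over an assumed range of both rates at the fixed 190 infants, along the lines of the table above.

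The cost is rewording. No infants are added and no analysis changes. The drawback is that the stated power becomes a range that looks less favourable under some assumptions.

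### The 20% loss allowance multiplies 79 by 1.2 when it should divide by 0.8, so 95 per group leaves 76 evaluable, fewer than the 79 needed for 90% power

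*Protocol article*

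**What the plan says.** The whole calculation is in section 3.10 (Sample size) of the protocol article. It sets the error rates ("The test level α is 0.05" and "the statistical power is (1- β) is 0.9") and takes from the literature improvement rates of about 90% with ear molding and about 70% without intervention. From these it concludes: "The sample content was calculated to be 79 cases per group".

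It then makes one adjustment: "According to the possible loss of follow-up of 20%, the sample was expanded to 95 cases in each group", which gives 190 in total. The section does not state the sidedness of the test, the sample size formula or the inflation formula, and it gives no other reason for 95.

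**The concern.** A loss to follow-up of 20% is a fraction of those randomised. To end with 79 evaluable infants per group, the number randomised must be 79 divided by the retained fraction, 0.8. Multiplying 79 by 1.2 always gives too few, because the 20% is then taken from a larger number than the one it was added to.

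The enrolment target of 190 rests on this step. If the step is wrong, the design does not deliver its stated power at its stated loss rate, and a reader who recomputes the three printed figures will find that they disagree.

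**Working it through.** **Inputs, all from section 3.10:** α = 0.05; power 0.90; rates 0.90 and 0.70; 79 per group before loss; loss 20%; 95 per group and 190 in total after the allowance. One assumption is needed to reproduce 79: a two-sided test, which the section does not state.

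**Step 1. Reproduce 79.** Normal approximation with unpooled variance:

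n = (z₀.₉₇₅ + z₀.₉₀)² × [p₁(1 − p₁) + p₂(1 − p₂)] / (p₁ − p₂)²

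= (1.960 + 1.2816)² × (0.09 + 0.21) / 0.20² = 78.8, rounded up to 79.

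The arcsine formula gives 79.0. Other common choices do not give 79: the two-sided pooled formula gives 82, or 92 with continuity correction, and the one-sided pooled formula gives 67, or 77 with continuity correction. The 79 is therefore sound under a two-sided test.

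**Step 2. Reproduce 95.**

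- Adding 20%: 79 × 1.2 = 94.8, rounded up to 95. This is the printed figure.
- Allowing for 20% loss: 79 / (1 − 0.20) = 98.75, rounded up to 99 per group, or 198 in total.

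The printed figure is short by 99 − 95 = 4 per group, or 8 in total.

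**Step 3. What 95 per group delivers.**

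- Evaluable at 20% loss: 95 × 0.8 = 76, which is 3 per group below 79.
- Largest loss that still leaves 79: 1 − 79/95 = 16/95 = 16.8%.

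**Step 4. Power at 76 beside power at 79.** With the unpooled formula, power = Φ(0.20 / √(0.30/n) − 1.960).

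- n = 79: Φ(3.246 − 1.960) = 90.1%
- n = 76: Φ(3.183 − 1.960) = 88.9%

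| Method | Power at 79 | Power at 76 |
|---|---|---|
| Unpooled | 90.1% | 88.9% |
| Arcsine | 90.0% | 88.9% |
| Pooled | 88.9% | 87.7% |
| Exact enumeration of the chi-square test | 90.2% | 89.0% |

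Within any one method the loss is 1.1 to 1.2 points. The 87.7% must be read beside its own 88.9% at 79. The rest of its distance from 90% comes from changing the formula and has nothing to do with the loss allowance.

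**The case against.** The strongest objection concerns weight, since the arithmetic is not in doubt. Three evaluable infants per group and just over one point of power will not change how the trial is run or read. The inputs are softer than that: both rates are given as approximate and the loss only as possible. If the molding rate were 89% instead of 90%, unpooled power at 79 per group would fall from 90.1% to about 86%, more than three times the effect at issue here. If actual loss is 16.8% or less, 95 per group is enough. All of this stands, and it limits how much should be made of the point.

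Two further defences do not rescue the 95.

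- **The sponsor may have meant only a 20% add-on.** The section ties the expansion to loss to follow-up. If an add-on was meant, the loss it covers is 16.8%, and the sentence still needs correcting.
- **The intention-to-treat analysis in section 3.12 (Statistical analysis) may keep lost infants in the comparison, with details in a plan not shown.** Section 3.10 itself treats lost infants as unavailable, which is why it inflates at all. The primary outcome is scored from follow-up photographs (section 3.8.1), so an infant lost before follow-up has no observed outcome, and section 3.12 states no imputation rule.

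Nor does this depend on the unstated sidedness or formula: the inflation step uses only the printed 79, 20% and 95.

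**Conclusion.** The concern holds. The inflation step in section 3.10 is wrong, while the step before it, from the rates and error levels to 79, is right under a two-sided test. As printed, 190 randomised, 20% loss and 90% power are incompatible. At 20% loss the design leaves 76 per group and about 89% power. To keep 79 it would need 99 per group.

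The shortfall is 4 randomised infants per group (8 in total), 3 evaluable infants per group at 20% loss, and about 1.1 points of power by the formula that gives 79. The counts follow from the section's own figures alone. The power figures also take the 90% and 70% rates at face value and assume a two-sided 0.05 test. This is a small, certain error in a figure the enrolment target rests on. It should be corrected, but it does not threaten the trial.

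**What to change.** Correct the last sentence of section 3.10. Without changing enrolment, it could read:

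> With 95 infants randomised per group (190 in total), at least 79 per group remain evaluable if loss to follow-up does not exceed 16.8%; at 20% loss, 76 per group remain and power is about 89%.

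This costs one sentence and a slightly lower stated power. It would help to name the two-sided test and the formula in the same place, so that the 79 can be checked.

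If the sponsor prefers to keep 90% power at 20% loss, the figures become 99 per group and 198 in total, at the cost of eight more infants. The size of the shortfall does not by itself require that.

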### Data management

3.11

The data will be recorded in the CRFs and input into an online database within 2 days of the follow up, which include participant demographics, disease histories, physician assessment of improvement, parents’ self-administrative questionnaires of HADS and 12-item short form survey of quality of life of quality of life. CRFs will be input into the database by 2 independent persons and cross-checked. The database will be locked when data input is finished and checked for data analysis by a biostatistician not aware of the group allocation of patients. The participants data will be protected and only used for this study. Personal information of participants will be kept confidential and anonymous data will be used for analysis. The principle investigator has access to the final trial dataset.

### Statistical analysis

3.12

For descriptive analysis, mean and standard deviation will be used for symmetric continuous variables, while median, first quartile, and third quartile will be used for asymmetric continuous variables. Frequency and percentage will be used to describe categorical variables. In baseline analysis of comparability between groups, analysis of variance will be used for continuous variables and Chi square test will be used for categorical variables.

The primary outcome improvement rate will be compared between groups and risk ratio with 95% confidence interval will be estimated using multi-level modelling adjusting for individual and hospital level factors. For secondary outcomes, mean difference with 95% confidence interval of WP CAD index score, parents’ evaluation of improvement (visual analogue scale), anxiety and depression, quality of life using multi-level modelling. Potential confounding factors at individual and study site level, and secular trend will be included/adjusted in the models. Intent to treat analysis will be conducted for the effectiveness analysis. Sensitivity analysis will be carried out using per protocol analysis. The significant level will be at 0.05. Statistical analysis will be performed using Stata 15.0 SE and MLN.

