### Control

3.6

The control group will be waiting list and receive usual neonatal care. Participants will be followed up at the same intervals as the intervention group until the sixth week after birth. After that, participants will be offered ear molding treatment as the same as the intervention group according to parents’ will, if the participant is not recovered spontaneously.

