### Treatment monitoring and discontinuation

3.7

Since the starting of ear molding, participants will be seen once a week by the responding health professional to check and assure the mold is in the right place. Any adverse events will be treated and medical advices will be given accordingly, including suspension or discontinuation of ear molding. Other treatments of CAD received by the participants will be asked and recorded in the case record form (CRF) at each point of follow up. Vouchers will be offered to participants who complete follow up.

Participants can withdraw from the trial on any reason, which will not affect their treatments or usual care. In addition, patients who withdraw due to adverse events will be treated and monitored until recovery.

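### Per protocol is a poor sensitivity analysis at 12 weeks, because control infants may by then have been molded for lack of recovery

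*Protocol article*

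**What the plan says.** Section 3.12 (Statistical analysis) of the protocol article takes intention to treat as the effectiveness analysis and then says: "Sensitivity analysis will be carried out using per protocol analysis". That is the only sensitivity analysis named, and the per-protocol set is not defined.

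Four other sections bear on it:

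- **3.6 Control.** Controls are followed to the sixth week of life. After that, parents may choose molding "if the participant is not recovered spontaneously".
- **3.8.2 Secondary outcomes, time of measurement.** The primary and secondary outcomes are taken 3 weeks and 12 weeks post-treatment.
- **3.7 Treatment monitoring and discontinuation.** Other treatment of the deformity is recorded at every follow-up. The section does not prohibit it.
- **3.10 Sample size.** The rates are 90% with molding and 70% without, and 20% loss to follow-up is allowed for.

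**The concern.** A sensitivity analysis should show whether the main result survives a change in an assumption that could be wrong. A per-protocol set selects infants by what happened after randomisation. In this trial a control infant becomes eligible for molding by doing badly on the feature being measured. Leaving such infants out of the control group at 12 weeks leaves a group enriched for natural recovery. Keeping them in means that the per-protocol and intention-to-treat results share the same late treatment of controls, so agreement between the two says nothing about it.

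Infants with no outcome cannot contribute to a per-protocol comparison either, so the expected loss also goes untested. A reader could take a discordant per-protocol result as evidence against a true effect, or a concordant one as reassurance that it cannot give.

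**Working it through.** **Timing.** Molding starts in the first 3 days of life and lasts 2 weeks (3.5). The 3-week assessment therefore falls at about week 3 of life if counted from the start of treatment, or week 5 if counted from its end. Both precede the offer to controls. The 12-week assessment falls at about week 12 or week 14, and both follow it. The mechanism in 3.6 thus reaches the 12-week assessment only. Before week 6, only treatment obtained elsewhere could matter.

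**The plan's own figure.** With two-sided α 0.05, power 0.9 and unpooled variance, n = (1.960 + 1.282)² × (0.9×0.1 + 0.7×0.3) / 0.2² = 78.8, so 79 per group, as stated. Then 79 × 1.2 = 94.8 gives the stated 95.

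**If molded controls are excluded.** Let p be the natural improvement rate and f the share of non-improved controls who are molded and dropped. The documents give no value for f, so it is varied. The per-protocol control rate is p / [p + (1 − p)(1 − f)]. With p = 0.70 this equals 0.70 / (1 − 0.30f). The molding arm is held at 90%.

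| f | Control rate | Difference (points) | Risk ratio |
|---|---|---|---|
| 0 | 70% | 20 | 1.29 |
| 1/3 | 0.70/0.90 = 77.8% | 12.2 | 1.16 |
| 1/2 | 0.70/0.85 = 82.4% | 7.6 | 1.09 |
| 2/3 | 0.70/0.80 = 87.5% | 2.5 | 1.03 |
| 0.741 | 90.0% | 0 | 1.00 |
| 1 | 100% | −10 | 0.90 |

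The zero point solves p / [p + (1 − p)(1 − f)] = 0.90, which gives f = 1 − p(1/0.9 − 1)/(1 − p). At p = 0.70 this is 0.741, or 0.741 × 0.30 × 79 = 17.6 of 79 controls excluded. The Introduction ties 70% natural recovery to one year of age, so the rate when parents choose may be lower. At p = 0.50 or 0.30 (assumed), the zero point moves to f = 0.889 or 0.952.

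At f = 1/2, power with 79 against about 67 infants is about 27%. With 79 per group and 90% against 70% it is about 89% (pooled-variance power function for both).

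**If molded controls are kept.** Let e be the success rate of late molding (assumed). The 12-week control rate is 0.70 + 0.30fe, in the per-protocol and the intention-to-treat analysis alike.

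- f = 0.74, e = 0.5: 0.70 + 0.111 = 81%, risk ratio 0.90/0.811 = 1.11.
- f = 0.74, e = 0.9: 0.70 + 0.200 = 90%, risk ratio 1.00.

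**Loss to follow-up.** 20% of 95 is 19, leaving 76 observed per arm. As an illustration, suppose lost infants improve at 50% (molding) and 90% (control), both assumed and deliberately adverse.

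- Molding: (0.9×76 + 0.5×19)/95 = 82%.
- Control: (0.7×76 + 0.9×19)/95 = 74%.

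The difference among all randomised infants is 8 points, while the observed infants still show 20.

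**The case against.** A reader might infer that the plan excludes molded controls and so will erase the effect. The documents do not say that. The per-protocol set is undefined, and molding after week 6 is part of the control strategy, so a literal per-protocol set could keep these infants. Such a set might still usefully drop ineligible infants or those who did not complete molding. Erasure also needs about 74% uptake at the plan's rates, more if natural recovery is lower, and no uptake figure is given. These points stand, and the exclusion result is therefore conditional.

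Nor does the text support reading the bias into the whole trial. The main analysis is intention to treat. The 3-week assessment precedes the offer, and nothing says that outside treatment depends on non-recovery. In the molding arm, dropping infants who stop early could push the result the other way. The documents give no rate for that and do not show that stopping predicts failure, so the offset is not quantified.

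Intention to treat with a per-protocol companion is conventional, and a condensed article may leave the set definition and missing-data analyses to a fuller document. Their absence is not the complaint. The article does commit to per protocol in the role of sensitivity analysis, and in that role it fails at 12 weeks under either reading.

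**Conclusion.** The point holds for the 12-week assessment, as a weakness of the stated sensitivity analysis rather than of the main analysis. If molded controls are excluded, the analysis selects on the outcome against molding. The 20-point difference becomes 12 to 2.5 points when one third to two thirds of non-recovered controls are molded, and zero at about 74%. If they are kept, the analysis does not test the crossover, and its 12-week contrast is diluted just as the intention-to-treat contrast is. Under either reading it cannot test the 20% expected loss.

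The figures rest on the plan's 90% and 70%, on assumed uptake, and on treating not recovered at the offer as not improved at 12 weeks. If some excluded infants would have recovered naturally in between, the bias is smaller.

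**What to change.** 1. Label per protocol as supplementary, and state how molding of controls after week 6 is treated in it.
2. Base the sensitivity analyses on all randomised infants:
   - (a) For controls molded before the analysed visit, whether in the trial or elsewhere, use the last score before molding, with not improved as a bound. State that both assume no later natural recovery and so favour molding. The bound returns the 70% control rate in the model above only because the model assumes that these infants would never have improved.
   - (b) Vary the improvement rate of lost infants separately by arm, by delta adjustment or a tipping-point analysis.
3. Reconcile the follow-up to week 6 in 3.5 and 3.6 with the 12-week outcome in 3.8.2.

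The cost is analysis wording, a little extra programming and an assumption that must be stated. Other treatment of the deformity is already collected at each follow-up. It should be confirmed that the start date of any molding in controls is recorded too.
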